## **6.2 Per protocol set (PPS)**

The PPS consists of all randomized subjects without any major deviations from the protocol. The following deviations in randomized subjects will lead to exclusion from the PP population. The primary analyses will be repeated in the PPS to support the primary results.

The following deviations will lead to exclusion from the PP population:

1. Subjects not receiving the assigned treatment as allocated by the EDC or no treatment at all;
2. Non-compliance to study drug. Non-compliance is defined as taking less than 80% of dispensed tablets based on manual pill bottle count at each study visit.
3. Patients with overdue AMCE or gastroscopy examination at visit 3 (180 days  $\pm$  2 weeks after randomization).

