### **5.5.2 Methods for breaking the blinding in the study**

In the event of a medical emergency, in which knowledge of the investigational drug is critical to the subject's medical management, the blind for that subject may be broken by the treating physician. Before breaking the blinding, the consent of the research leader of the participating research site should be obtained and the relevant researchers and monitors should be informed. At the same time, the events leading to break the blinding and the blind code information should be recorded in detail. After breaking the blinding, the subject will not receive any study drug, and the treated physician can take corresponding bail-out measures according to local standard of care. The study drugs cannot be resumed even if the condition of subject is stable, while researchers still need to conduct clinical follow-up for 12 months for the subject with broken blinding, and AMCE examination is still required. Researchers should withdraw the study drugs from the patients whose blinding was broken.

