### **6.2.2 Face-to face follow-up procedure at 6 months**

- Assess for adverse events may include, but not be limited to MI, stroke, revascularization, bleeding and ST
- Review concomitant medications with subject
- Counsel subject about importance of study drug compliance
- Assess for randomization eligibility – If applicable:
  - Randomize subjects via the Taimei Medical Randomization and Drug Management System (eBalance), and obtain container/kit number
  - Conduct the second AMCE examination to observe gastrointestinal mucosal lesions
  - Dispense study medications for next 6 months
  - Schedule next clinic visit at 12 months (for randomized subjects)
- Instruct the subject and/or caregiver to notify the investigator of any occurrence of adverse events

- Instruct the subject to return study drugs at next time of in-clinic face-to-face visit

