## **18.2 The treatment procedure of clinically-driven or AMCE-positive gastrointestinal (GI) bleeding**

- 1) The patient with GI bleeding before randomization will be treated in accordance with the following (Appendix 1-3) rules. The patient will be no longer randomized and the study is terminated.
- 2) The patient with GI bleeding after randomization should be confirmed by gastroscopy, and endoscopic treatment is taken if necessary. If the lesion is not clear, the AMCE examination is performed to observe the small intestine lesions. If no clear bleeding is found, colonic bleeding is suspected, and further colonoscopy should be performed.
- 3) After obtaining the consent of principal of the participating research site, the treating physician could unblind for this patient (Part 5.4), conduct hemostatic treatment and adjust antiplatelet therapy according to the following rules (Appendix 1-3). Antiplatelet therapy could be at physician's discretion according to local standard care after curing the bleeding.
- 4) This patient will not terminate study, but only clinical 12-month follow-up (without AMCE examination) is needed.

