## 4 Primary and secondary variables

### 4.1 Primary variable

The primary endpoint is the incidence of gastric or intestinal mucosal injury occurring within 12 months after enrollment, defined as erosion, ulceration or bleeding detected by either planned AMCE or clinically-driven endoscopy. Specifically, gastrointestinal erosion is defined as superficial mucosal breaks with a diameter of  $<5$  mm.

Gastrointestinal ulcer is defined as a mucosal break with a diameter  $\geq 5$  mm, typically covered with fibrin.

Situations below can be regarded as valid primary endpoint results, including:

- Successful completion of the AMCE examination at 6 months after randomization (i.e., 12 months after enrollment), regardless of the results of examination;
- Although the third AMCE examination at 6 months after randomization is not done, the second examination at 6 months after PCI reports new-onset gastric or small intestinal mucosal lesions;
- AMCE or gastroscopy examination driven by the occurrence of gastrointestinal bleeding at any time during the whole study period observes new-onset gastric or small intestinal mucosal lesions.

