## **9.7 Investigational medication compliance**

Compliance will be assessed by the investigator and/or study personnel at each visit using pill counts and information. Study drug accountability will be determined by the site monitor while performing routine site visits and at the completion of the study.

Study drug compliance will be assessed using manual pill count at the 12-month in-person follow-up visit. The percentage of study drug compliance for the overall treatment period will be derived for each patient based on pill counts as the number of pills taken (dispensed – returned), relative to the expected number of pills taken. Study drug compliance will be presented descriptively, including mean, median, quartiles and 5% and 95% percentiles.

*Non-compliance is defined as taking less than 80% of dispensed tablets based on manual pill bottle count. The non-compliance patients will exclude from the PP population.*

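### The per-protocol compliance rule counts tablets against the full six-month supply, so a patient stopped early because of a lesion-confirmed GI bleed leaves the PPS because of a primary-endpoint event

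*Supplement*

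**What the plan says.** **PPS rules.** SAP 6.2, like protocol 12.1, removes a randomised patient for non-compliance: "Non-compliance is defined as taking less than 80% of dispensed tablets based on manual pill bottle count at each study visit". SAP 9.7 restates the threshold and adds: "The non-compliance patients will exclude from the PP population". Neither section exempts a stop caused by an adverse event or an endpoint. A further rule in SAP 6.2 excludes "Patients with overdue AMCE or gastroscopy examination at visit 3", with a window of 180 days ± 2 weeks after randomisation.

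**Denominator.** The exclusion rule divides by dispensed tablets. The descriptive compliance percentage in SAP 9.7 is instead taken "relative to the expected number of pills taken". Protocol 6.2.2 has the site "Dispense study medications for next 6 months" at the randomisation visit, so dispensed means the whole course.

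**What happens after a bleed.** Protocol 18.1 requires immediate unblinding after randomisation when repeated positive fecal occult blood tests come with a hemoglobin drop. Protocol 18.2 permits unblinding, with site consent, for clinical or capsule-detected GI bleeding. Protocol 5.5.2 gives the consequence: "After breaking the blinding, the subject will not receive any study drug". The same section and SAP 3.4.2 bar resumption.

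**Status of the event.** SAP 4.1 accepts as a valid primary-endpoint result "AMCE or gastroscopy examination driven by the occurrence of gastrointestinal bleeding at any time during the whole study period observes" new gastric or small-intestinal lesions. SAP 6.1 counts events in the FAS whether they came before or after study drug was stopped.

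**The concern.** A patient can do everything the protocol asks, have a primary-endpoint event, have study drug withdrawn because of it, and then be classed as a major deviator. PPS membership then depends on a post-randomisation variable that the outcome itself caused.

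SAP 9.2 repeats the primary analysis in the PPS to support the main result, and SAP 9.3.2 repeats the secondary analyses there. If the trial hypothesis is right and DAPT injures the gut more, the rule may take a larger share of events from the DAPT arm. A weaker PPS estimate could then be misread as an effect of adherence when part of it comes from the exclusion rule.

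**Working it through.** **1. Reproduce the plan's figure.** Inputs from SAP 5: 47% vs 30%, monotherapy to DAPT 2:1, two-sided 0.05, power 90%. The pooled rate is (0.47 + 2 × 0.30)/3 = 0.3567.

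DAPT patients = [1.960 √(0.3567 × 0.6433 × 1.5) + 1.282 √(0.47 × 0.53 + 0.30 × 0.70/2)]² / 0.17² = 126.6, so 127, and 381 in total against the stated 384. With 128 and 256 the power is 90.3%. The design reproduces; base difference 17.0 points, OR 0.483.

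**2. When the rule bites.** Taking six months as 180 days with full adherence until the stop, 0.80 × 180 = day 144. An earlier stop is excluded; a later one passes the 80% rule.

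**3. Effect on the PPS rates.** Let b be the share of an arm with a lesion-confirmed, bleed-related stop and f the fraction of those stops before day 144. The removed share is x = b × f, and the PPS rate is (p − x)/(1 − x). The documents give neither b nor f, so both are assumptions. Events removed are 128x (DAPT) and 256x (monotherapy).

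| b, DAPT / mono | f = 0.8: difference, OR | f = 0.8: events removed | f = 1: difference, OR | f = 1: events removed |
|---|---|---|---|---|
| 1% / 0.5% | 16.9, 0.485 | 1.0 / 1.0 | 16.8, 0.486 | 1.3 / 1.3 |
| 2% / 0.5% | 16.4, 0.494 | 2.0 / 1.0 | 16.3, 0.496 | 2.6 / 1.3 |
| 3% / 1% | 16.3, 0.496 | 3.1 / 2.0 | 16.1, 0.499 | 3.8 / 2.6 |
| 5% / 2% | 15.9, 0.500 | 5.1 / 4.1 | 15.6, 0.505 | 6.4 / 5.1 |
| 8% / 3% | 15.1, 0.515 | 8.2 / 6.1 | 14.6, 0.524 | 10.2 / 7.7 |

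Example, 5% / 2% with f = 1: (0.47 − 0.05)/0.95 = 44.2% and (0.30 − 0.02)/0.98 = 28.6%, a difference of 15.6 points.

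**4. Direction.** The PPS difference equals 0.70/(1 − x_mono) − 0.53/(1 − x_DAPT). For small x it shrinks only if x_DAPT exceeds x_mono by a factor above 0.70/0.53 = 1.32. The OR moves toward 1 only if the factor exceeds 0.47/0.30 = 1.57. With equal removal of 5% / 5% and f = 1, the difference grows to 17.9 points (44.2% vs 26.3%). The bias toward no difference is therefore conditional on the arms' bleed rates.

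**The case against.** The strongest reply is that few patients are affected and nothing primary depends on them. Most primary events should be erosions or ulcers seen at a planned examination with no drug stop. SAP 3.2 and 3.3 screen out recent GI bleeding or ulcers and any ulceration or bleeding at the 6-month examination, and SAP 1.1 notes low major bleeding rates in most prior studies. The FAS/mITT analysis keeps these events, and SAP 8 adds complete-case, best-case, worst-case and tipping-point analyses. An 80% pill count is also a conventional threshold. All of this stands. It limits the size but does not remove the rule's dependence on the outcome.

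Four stronger readings are tempting and are not supported.

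- *The overdue-examination rule removes the same patients as well.* It speaks of an overdue examination, not a waived or missing one. Whether an examination is due is itself unsettled: protocol 18.2 says "This patient will not terminate study, but only clinical 12-month follow-up (without AMCE examination) is needed", while protocol 5.5.2, protocol 5.9.2 and SAP 3.4.2 still require the examination after unblinding or discontinuation.
- *Every bleeder is lost.* Unblinding is mandatory only on the occult-bleeding pathway. Late stops pass the rule, and a bleed with no lesion found is not clearly a primary event. If expected pills in SAP 9.7 ended at the stop date, that percentage would spare these patients, but the exclusion rule is written on dispensed tablets.
- *DAPT loses many more events.* This holds as a proportion. Under 2:1 pooling the counts can be close or equal, as the table shows.
- *The PPS is worthless as a check.* Where the bias is toward no difference, a PPS result that still agrees with the FAS is conservative support.

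**Conclusion.** The point holds for one group: randomised patients with a lesion-confirmed GI bleed whose study drug is stopped before about 80% of the six-month supply is used. The written rule classes them as non-compliant and drops a valid primary-endpoint event because of that event.

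Over the assumed rates, the PPS difference moves from 17.0 points to about 16.9 (1% vs 0.5%, 80% of stops early) down to 14.6 (8% vs 3%, all early), and the OR from 0.483 to between 0.485 and 0.524. These rates are illustrations and not document figures. The direction rests on the DAPT removal rate being at least about 1.3 times (difference scale) or 1.6 times (OR scale) the monotherapy rate. The damage is confined to supportive analyses; the primary FAS/mITT conclusion does not change. The rule is worth mending because the mend is nearly free.

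**What to change.** In SAP 6.2 and 9.7:

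1. Define compliance as tablets taken divided by tablets expected from randomisation up to the earliest of three points: the first bleed-driven primary-endpoint event after randomisation, the unblinding or stop that the bleeding rules lead to, or visit 3. Use this one denominator for both the description and the exclusion.
2. Still exclude anyone below 80% before that point. Do not keep patients solely because they had an event: retaining non-compliant patients with events while dropping those without would select on the outcome in the other direction.
3. Apply the overdue-examination rule only to patients who do not already hold a valid primary-endpoint event from a bleed-driven examination after randomisation. Saying after randomisation matters, because SAP 4.1 can also count lesions from the 6-month examination, which precede the randomised drug.
4. Tabulate PPS exclusions by reason and arm.

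Protocol 18.2 must also be reconciled with protocol 5.5.2 and 5.9.2 and SAP 3.4.2 on whether capsule endoscopy follows a bleed.

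The cost is a few sentences, a small change to the PPS derivation and one table. No new data are needed: protocol 5.9.2 already records the stop date and has the remaining tablets returned. No treatment rule changes, and the primary analysis is untouched.

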## **6.3 Safety analysis set**

There are 2 safety sets (SSs) in OPT-PEACE trial. Safety and tolerability will be assessed from serious adverse events (SAEs) and adverse events (AEs). The assessment will include MACCE defined as a composite of cardiac death, target lesion MI, ischemic stroke, clinical-driven TLR or stroke in SS (investigational drug) and the incidence of AEs related to AMCE examination and capsule retention in SS (AMCE examination). All events will be independently adjudicated.

The first safety analysis set includes patients who received at least 1 dose of study drugs (aspirin, clopidogrel, and/or matching placebos) and who have data observed at any time after first randomized dose until the end of the study. The safety endpoint is MACCE defined as a composite of cardiac death, target lesion MI, ischemic stroke, clinical-driven TLR or stroke within 12 months after enrollment. Throughout the safety results sections, erroneously treated patients (patients randomized to one of the treatment groups but actually given the other treatment) will be accounted for in the actual treatment group. Patients with erroneous treatment would be analyzed according to that treatment only if they only received the erroneous treatment and none of the correct treatment.

The secondary safety analysis set includes patients who received AMCE exam at least once and observed up to 30 days for safety surveillance. The safety analysis set will be considered the primary analysis set for AMCE as a method for detecting gastrointestinal mucosal injury and bleeding. The safety endpoint is 1) adverse events, defined as symptoms or signs such as abdominal distension, nausea, or vomiting; 2) capsule retention (i.e., a capsule endoscope remaining in the digestive tract for a minimum of 2 weeks or a capsule endoscope that requires directed intervention or therapy to aid its passage).

All safety variables will be analyzed using the safety analysis set.

## 7 Subgroups

The primary and secondary endpoints will be also analyzed in the following clinically relevant pre-specified subgroups.

- Age (<65 years, ≥65 years)
- Sex (male, female)
- Diabetes mellitus (yes, no)
- Chronic kidney disease (eGFR<60, ≥60 mL/min/1.73m^2)
- Acute coronary syndrome (yes, no)

- Prior history of gastrointestinal bleeding (<24 months,  $\geq$ 24 month)
- HP infection status (yes, no)\*
- DAPT duration prior to randomization (>6 months,  $\leq$ 6 months)

Another subgroup analysis will be performed in patients in whom follow-up was complete vs incomplete or otherwise affected by the COVID-19 pandemic (6-month visit after randomization date: before 2020/1/23, after 2020/1/23).

*\*A HP breath test will be performed after the screening AMCE exam to document HP infection status. HP eradication therapy is not mandatory but is allowed per physician discretion.*

## **8 Lost to follow-up and missing data**

In keeping with an intent-to-treat philosophy, the primary analyses are performed on all randomized subjects. We anticipate that the amount of missing data will be minimal in the present study as we are specifically asking sites to ensure that the data elements are complete. No imputation will be carried out for missing baseline data.

If outcome data are missing, to assess the potential impact of missing data, a sensitivity analysis will be conducted which will include a complete case (including only subjects whose AMCE outcome is known at 6 months after randomization), a best-case (assume missing subjects in monotherapy group are event free at 6 months and missing subjects in DAPT have gastric or intestinal mucosal injury at 6 months), a worst-case (assume missing subjects in monotherapy group have gastric or intestinal mucosal injury at 6 months and missing subjects in DAPT group are event free at 6 months), and a tipping point analysis if the conclusion is changed in the worst-case analysis.

## 9 Statistical methods

### 9.1 General principles

Statistical analyses will be performed using SAS version 9.3. Unless otherwise stated, all hypothesis tests will be performed using two-sided tests at the 5% significance level. Data will be summarised overall and by treatment group. Continuous variables will be summarised as the number of observations, number of missing values, mean, standard deviation, median, quartiles, and range. Categorical variables will be summarised as the number of observations, number of missing values, frequencies, and percentages. Baseline clinical, demographic, laboratory and procedural characteristics will be summarized by randomized treatment group.

### 9.2 Analysis for the primary endpoint

The primary objective of OPT-PEACE trial is to determine the impact of 6-month DAPT plus 6-month single antiplatelet therapy versus 12-month DAPT in terms of the primary endpoint (gastrointestinal injury) after contemporary DES implantation. This analysis will be carried out in the FAS. The null hypothesis ( $H_0$ ) for this analysis is that the incidence of primary endpoint in the experimental group is same as that of the control group, namely  $P_0=P_1$ . The alternative hypothesis ( $H_1$ ) is that the incidences of primary endpoints in the two groups was not equal, namely  $P_0 \neq P_1$ , and the superiority test is conducted at the 2-sided significance level of 0.05. An odds ratio (OR) and two-sided 95% CI for the primary endpoint will be generated using the logistic regression model with treatment (monotherapy group vs. DAPT group) as fixed effect factors. This analysis will be repeated in the PPS to support the main results.

In addition, for the purpose of exploration, primary endpoint will also be compared across the 3 groups, and for all single group versus group comparisons (12-month DAPT vs 6-month DAPT plus 6-month aspirin monotherapy; 12-month DAPT vs 6-month DAPT plus 6-month clopidogrel monotherapy; and 6-month DAPT plus 6-month aspirin monotherapy versus 6-month DAPT plus 6-month clopidogrel monotherapy).

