### **5.5.1 Methods for ensuring blinding**

This study has a double-blind design with aspirin, clopidogrel, and matching placebos. Shenyang Yu Kang Pharmaceutical Technology Co., Ltd, a statistical organization independent of the study, used SAS software to generate random codes for the corresponding groups (primary blind codes), and the study drug regimen corresponding to the group (secondary blind codes), and import the two levels of blind codes (including primary and secondary blind codes) via the Taimei Medical Randomization and Drug Management System (eBalance). Randomization is stratified according to site and will be performed in fixed block. The active tablets and the respective placebo tablets will be identical in size, color, smell, and taste. The patients, site personnel, sponsor personnel, persons performing the assessments, and data analysts will remain blinded to the identity of the treatment from the time of randomization until completing the statistical analysis. There will be an independent data safety monitoring board (DSMB) to monitor the data on a periodic basis.

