| Protocol synopsis             |                                                                                                                                                                                                                                                                                                       | Updated                                                                                                                                       |                                                                                                                                                                         |
|                               | Study centers: 26 sites in China                                                                                                                                                                                                                                                                      | Study centers: 27 sites in China                                                                                                              | The participating sites have been changed.                                                                                                                              |
| 3. study design and flowchart |                                                                                                                                                                                                                                                                                                       | Study flowchart updated                                                                                                                       |                                                                                                                                                                         |

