### **3.3 Subject randomization**

The eligibility for randomization for all enrolled patients will be evaluated at 6 months (±2 weeks), including medication adherence and the interval occurrence of adverse events. The patients with any of the following will not be randomized:

- (1) Withdrawal of informed consent;
- (2) Lost to follow-up at 6 months;
- (3) Any event in the prior 6 months which in the opinion of the investigator results in the patient not being suitable for randomization of antiplatelet agent regimen either because of a) necessity to continue dual antiplatelet therapy (eg, major adverse cardiovascular or cerebrovascular event within the prior 6 months or need for repeat stenting), or b) inability to continue dual antiplatelet therapy (eg, bleeding, neoplasm, need for urgent surgery, etc within the prior 6 months);
- (4) Not presently taking both aspirin and clopidogrel, or any prior temporary discontinuation of aspirin or clopidogrel for  $\geq 5$  days;
- 5) Use of proton pump inhibitors or gastric mucosal protectants for more than 12 days, or for more than 4 continuous days in the 6 months prior to randomization\*;
- (6) Unwillingness or inability to undergo the 6-month AMCE examination or the remainder of the study procedures, including the 12-month AMCE exam.

At this time patients free from interval major adverse ischemic or clinically overt bleeding events and otherwise without any above-mentioned exclusion criteria will undergo a second AMCE examination before randomization. Patients successfully completing 6-month follow-up AMCE exam and with no ulceration or bleeding are then randomly assigned in a 1:1:1 ratio to receive aspirin plus clopidogrel, aspirin plus clopidogrel-placebo or clopidogrel plus aspirin-placebo for an additional 6 months in a double blinded manner.

Randomization is stratified according to site and will be performed in fixed block of sizes 6 and block sizes will not be revealed to sites. The electronic data capture system (EDC) will be used to randomize subjects. The EDC will assign a treatment arm for patients and specify the appropriate medication number for the package of investigational treatment to be dispensed to the patient.

Enrolled patients who do not meet eligibility for randomization will not receive any more study drugs, and subsequent antiplatelet therapy will be administered at their attending physicians' discretion in accordance with the local standard of care. All

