## **5 Sample size**

The cumulative incidence of the primary endpoint of gastric or intestinal mucosal lesions within 12 months is estimated to be 47% in patients who received 12 months of DAPT and 30% in those treated with either aspirin or clopidogrel monotherapy beginning at 6 months after enrollment. With a 2:1 ratio in patients treated with either aspirin or clopidogrel monotherapy after 6-month DAPT versus DAPT for 12 months, 384 evaluable patients (256 and 128 respectively) provide 90% power to detect a 17% absolute risk reduction (36% relative risk reduction) with a 2-sided type I error of 0.05. Assuming 20% loss of evaluable primary endpoint outcome assessments due to patient withdrawal, loss to follow-up between 6 and 12 months or suboptimal AMCE visualization of the GI tract at 12 months, 480 patients are planned to be randomized. Assuming that an additional 10% of enrolled patients will not be randomized at 6 months because of adverse clinical events, noncompliance with antiplatelet therapy or lost to follow-up or withdrawal, 534 patients were initially planned to be enrolled after baseline screening. Finally, assuming that 10% of patients who undergo a screening AMCE examination will be excluded due to gastrointestinal ulcer or bleeding, approximately 593 patients were initially planned to be consented and undergo the screening AMCE examination.

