### 9.3.1 Analysis for categorical and ordinal endpoints

#### **Binary variables include:**

- The incidence and severity of gastric and intestinal mucosal lesions during the first 6 months after study enrollment (prior to randomization);
- The incidence and severity of gastric and intestinal mucosal lesions after randomization (ie, between 6 months and 12 months after study enrollment);
- The incidence of clinically evident gastrointestinal hemorrhage attributed to the upper GI tract (or of unknown origin) during 6 months after study enrollment (prior to randomization);
- The incidence of clinically evident gastrointestinal hemorrhage attributed to the upper GI tract (or of unknown origin) after randomization (ie, between 6 months and 12 months after study enrollment);
- The incidence of clinically evident gastrointestinal hemorrhage attributed to the upper GI tract (or of unknown origin) during 12 months after study enrolment.

Binary variables will be analyzed using logistic regression with treatment as fixed effect factors. Logistic regression model results will be reported as odds ratios for monotherapy group vs. DAPT group, with 95% CIs and p-values.

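### Randomisation is stratified by site, but the primary model contains treatment alone and yields no risk difference or risk ratio with a confidence interval

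*Supplement*

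**What the plan says.** **Randomisation.** SAP 3.3: "Randomization is stratified according to site and will be performed in fixed block of sizes 6". Protocol version 1.4, section 5.5.1, agrees on the stratification: "Randomization is stratified according to site and will be performed in fixed block". The revised description in the summary of protocol changes gives "Study centers: 27 sites in China".

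**Primary analysis.** The null hypothesis in SAP 9.2 "is that the incidence of primary endpoint in the experimental group is same as that of the control group", which is a statement about incidences. For the estimate, the same section says "An odds ratio (OR) and two-sided 95% CI for the primary endpoint will be generated". The model behind that estimate has no other term, since it is to be obtained "using the logistic regression model with treatment (monotherapy group vs. DAPT group) as fixed effect factors". SAP 9.3.1 treats the binary secondary endpoints in the same way: "Binary variables will be analyzed using logistic regression with treatment as fixed effect factors".

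**Planning scale.** In SAP 5 the 12-month incidence "is estimated to be 47% in patients who received 12 months of DAPT and 30% in those treated" with monotherapy from month 6. The stated target is a 17-point absolute (36% relative) reduction.

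**What else is planned.** SAP 9.8 on sensitivity analyses refers only to section 8, which deals with missing outcomes. SAP 9.1 calls for counts and percentages by treatment group, and the table list includes the 12-month frequency of injury. No site-stratified test, covariate-adjusted comparison, risk difference or risk ratio is specified.

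**The concern.** Blocking within site forces the arms to be balanced at each site. If sites differ in lesion rates, that balance makes the treatment comparison more precise than a model without site can recognise. The standard error is then too large, the test rejects less often than 5% under the null, and power is given away.

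Baseline information is left unused in the same way. Protocol 5.2 has every patient undergo a screening AMCE and an HP breath test. Only ulceration or bleeding bars enrolment, so erosion at screening varies among randomised patients and could serve as a covariate.

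The effect measure is a separate matter. A trial planned on an absolute difference would report its main result, with an interval, only as an odds ratio, for an outcome expected in 30% to 47% of patients. At such rates an odds ratio lies well away from the risk ratio.

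**Working it through.** **1. The plan's own figure.** Inputs from SAP 5: 47% and 30%, 128 DAPT and 256 monotherapy, two-sided alpha 0.05.
- Pooled rate = (128 × 0.47 + 256 × 0.30)/384 = 0.3567.
- Null SE = √[0.3567 × 0.6433 × (1/128 + 1/256)] = 0.0519.
- Alternative SE = √(0.47 × 0.53/128 + 0.30 × 0.70/256) = 0.0526.
- Power = Φ[(0.17 − 1.96 × 0.0519)/0.0526] = Φ(1.30) = 90.3%.

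The stated 90% is reproduced. The required total by the same formula is 381, against 384 stated, and 384/0.8 = 480 randomised also agrees.

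**2. Effect measures at the planned rates**
- Odds ratio = (0.30/0.70)/(0.47/0.53) = 0.48. SE of its log = √(1/76.8 + 1/179.2 + 1/60.16 + 1/67.84) = 0.224, so the 95% CI is about 0.31 to 0.75.
- Risk ratio = 0.30/0.47 = 0.64.
- Risk difference = −17 points, 95% CI −17 ± 1.96 × 5.26, about −27 to −7 points.

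The odds are reduced by 52% and the risk by 36%.

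**3. Effect of ignoring site.** The documents give no between-site variance, so a range was assumed. Each setting used 4,000 simulated trials:
- 480 patients at 27 sites of unequal size, in blocks of 6 within site (four monotherapy, two DAPT), with 80% evaluable.
- Normal site effects on the logit scale.
- Marginal rates of 47% and 30% for power, and 38.5% in both arms for test size.
- SAP 9.2 names no separate test, so the Wald test from the treatment-only logistic model was taken as the planned one.

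| Assumed site SD (logit) | Size, treatment only | Size, Mantel-Haenszel by site | Power, treatment only | Power, Mantel-Haenszel by site |
|---|---|---|---|---|
| 0 | 4.7% | 4.7% | 89.9% | 89.1% |
| 0.3 | 4.9% | 4.8% | 91.6% | 91.5% |
| 0.6 | 4.0% | 4.2% | 90.4% | 91.0% |
| 1.0 | 3.0% | 4.5% | 91.5% | 93.4% |

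The Monte Carlo SE is √(0.05 × 0.95/4000) = 0.35 points for size and about 0.5 points for power. Only at SD 1.0 does the treatment-only test fall clearly below both 5% and the stratified test.

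**4. One prognostic covariate, no site effect.** Its strength is also assumed.

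| Assumed covariate SD (logit) | Power, treatment only | Power, adjusted |
|---|---|---|
| 0.5 | 90.5% | 92.0% |
| 1.0 | 89.6% | 94.5% |

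The size of the adjusted test in these two settings was 5.7% and 5.9%, at the upper edge of simulation noise. With the same covariate and site SDs of 0.3 and 0.6 it was 4.5% to 5.0%.

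**5. Room for site terms.** 384/27 is about 14 evaluable patients per site. A logistic model with 26 site indicators would be unstable.

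**The case against.** The strongest reply is that nothing here threatens validity. The treatment-only test showed no inflation beyond simulation noise, power stays near 90%, and the gain from stratifying is nil at small site SDs. SAP 3.4.1 sends all AMCE images to one blinded core laboratory, which removes differences between site readers as a source of site variation. All of this stands and limits the point to efficiency.

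A reader might infer that the trial ignores known strong predictors. The documents do not support that. They give no strength for HP status or earlier lesions, and SAP 9.5 treats prediction as exploratory. The covariates are plausibly prognostic, no more.

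A reader might also expect the largest gain from adjusting for erosion at the 6-month AMCE. That covariate is not usable under the current endpoint: SAP 4.1 counts injury over the whole 12 months and accepts new lesions at the 6-month examination as a valid result.

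Nor is it right that only an odds ratio will be reported. Percentages by group are planned, so crude differences and ratios can be read off. What is missing is a confidence interval for either.

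Finally, adjustment has its own costs. SAP 8 rules out imputing baseline data, so patients with missing covariates would drop out of an adjusted model. A conditional odds ratio also lies further from the risk ratio than the unadjusted one. Both objections are fair, and the change to the SAP must deal with them.

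**Conclusion.** The mismatch is real and worth mending, but its consequence is modest. The analysis does not use the stratification factor, no adjusted analysis is planned, and the only interval is on the odds-ratio scale although the hypothesis and sample size are on the incidence scale.

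Under assumed site SDs of 0 to 1.0, test size runs from about 5% to 3%, and stratifying moves power by about -1 to +2 points. A baseline covariate with an assumed SD of 0.5 to 1.0 adds about 1.5 to 5 points. These ranges rest on assumptions, because the documents give neither site variance nor covariate strength. The contrast between an odds ratio of 0.48 and a risk ratio of 0.64 needs only the plan's own rates.

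A reader might conclude that the unstratified test raises the false-positive rate or that the sample size is wrong. Neither follows: the error is on the conservative side, and the stated power is reproduced.

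**What to change.** In SAP 9.2, name one site-stratified primary analysis in advance. Two choices are suitable:
- a Mantel-Haenszel analysis by site, with small sites pooled by a fixed rule; or
- logistic regression with a random site intercept, adjusted for screening-AMCE erosion, HP status and age, with a stated rule for missing covariates as an explicit exception to SAP 8.

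Do not use 26 site indicators, and do not adjust for 6-month AMCE lesions while they can count towards the endpoint. Report the risk difference and risk ratio with 95% CIs beside the odds ratio, standardised over the covariates if the regression is chosen. Carry the same approach into SAP 9.3.1 where event numbers allow.

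The cost is SAP wording and minor programming, with no new data. The regression option gives a conditional odds ratio that differs from the marginal one; the standardised risk difference returns the result to the scale of the hypothesis.
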